#### **4.4. Withdrawal and discontinuation**

If participants do not tolerate the trial procedure the investigator decides whether the participant should be excluded. Participants can at any time withdraw their informed consent to the study. Patients can be excluded from the study due to violation of inclusion criteria or meeting exclusion criteria which were not available at study entry. Withdrawal will be documented in the database with all other study data. If participants withdraw their informed consent to the study, their medical data as well as biological material (blood samples) collected until then, will be analysed and kept in a data blood bank (Biobank Department Endocrinology) in an encrypted/coded fashion. In case of an early study discontinuation, participants will be replaced according to the sample size calculation.

## **5 STATISTICS AND METHODOLOGY**

### **5.1. Statistical analysis plan and sample size calculation**

The null hypothesis is that the area under the concentration time curve of OT is equal for patients with central diabetes insipidus and healthy volunteers after a single dose of MDMA, i.e. the primary endpoint is zero. The alternative hypothesis is that the area under the concentration time of OT is lower in patients with central diabetes insipidus as compared to healthy volunteers, i.e. the primary endpoint is not zero.

The time course of OT measures after intake of MDMA and placebo will be visualized by means of line plots and boxplots for patients with central diabetes insipidus and healthy volunteers. Summary statistics (median, interquartile range, minimum and maximum value) will be presented for each measurement time of OT for MDMA and placebo for patients with central diabetes insipidus and healthy volunteers. Maximum OT time will be summarized for MDMA and placebo for patients with central diabetes insipidus and healthy volunteers separately by means of frequency distribution according to the measurement times, and by median, interquartile range, minimum and maximum value. OT area under the concentration time curve from baseline to 6 hours after intervention will be tested for a difference between MDMA and placebo for patients with central diabetes insipidus and healthy volunteers. Summary statistics (median, interquartile range, minimum and maximum value) will be presented separately.

All other secondary endpoints will be analyzed descriptively. The time course of MDMA, cortisol, prolactin, copeptin, and ACTH levels will be visualized by means of line plots and boxplots, and summary statistics will be presented for each measurement time for MDMA and placebo for patients with central diabetes insipidus and healthy volunteers separately.

Sample size was estimated in order to show a significant increase in OT after the intake of a single oral dose of MDMA with a power of 90 % and a significance level  $\alpha$  of 0.05. Sample size estimation was based on preliminary data from 28 healthy adults. In this trial, OT levels following MDMA intake was studied. The mean increase in OT levels for MDMA was 809+/-64 pg/mL and 259 +/- 62 pmol for placebo.

Assuming 30% reduced levels of OT after MDMA in patients with central diabetes insipidus as compared to healthy volunteers, a total of 15 subjects should be recruited in order to have N = 12 evaluable subjects, assuming a drop-out rate of 20 %.

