|                      |                                                                                                                                                                                                                                                                                                                                                                                                                                                                                                                                                                                                                                                                                                                                                                           |
|----------------------|---------------------------------------------------------------------------------------------------------------------------------------------------------------------------------------------------------------------------------------------------------------------------------------------------------------------------------------------------------------------------------------------------------------------------------------------------------------------------------------------------------------------------------------------------------------------------------------------------------------------------------------------------------------------------------------------------------------------------------------------------------------------------|
|                      | 
MDMA. Future studies could consider interventional studies using oxytocin application to reduce pathophysiology in patients with central diabetes insipidus and ultimately increase their quality of life.
 
The cross-over design with a washout period of at least two weeks is considered appropriate as first, no residual effects of MDMA is present after two weeks, second, the sample size is reduced as the inter-individual variability is reduced.
 
In order to increase the understanding of the pathophysiology of oxytocin and MDMA in patients with central diabetes insipidus it is crucial to compare the values to healthy controls. Only with these two study populations can we conclude how oxytocin is stimulated following MDMA.
 |

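### Section 5.1 claims 90% power for an oxytocin rise after MDMA; it does not show that power for the primary AUC comparison of patients with controls

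*Protocol*

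**What the plan says.** The sample-size text is in Protocol section 5.1 and is repeated in the synopsis row on number of participants.

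- Target: "Sample size was estimated in order to show a significant increase in OT after the intake of a single oral dose of MDMA". The same sentence goes on "with a power of 90 % and a significance level" and sets alpha, followed by the data source: "of 0.05. Sample size estimation was based on preliminary data from 28 healthy adults".
- Inputs: "The mean increase in OT levels for MDMA was 809+/-64 pg/mL and 259 +/- 62 pmol for placebo".
- Between-group effect: "Assuming 30% reduced levels of OT after MDMA in patients with central diabetes insipidus as compared to healthy volunteers".
- Result: "a total of 15 subjects should be recruited in order to have N = 12 evaluable subjects, assuming a drop-out rate of 20" %.

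The primary endpoint (section 3.2) is the oxytocin AUC from baseline to 6 hours after MDMA, taken against placebo in the same subject and compared between patients and healthy volunteers. The null hypothesis in section 5.1 is that this AUC is equal in the two populations. The alternative is that it is lower in patients "as compared to healthy volunteers, i.e. the primary endpoint is not zero". The synopsis plans 15 patients and 15 healthy volunteers, and section 5.2 replaces drop-outs until at least 30 subjects are reached.

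**The concern.** The sentence that carries the 90% figure concerns MDMA against placebo within a person. The next step brings in a 30% difference between two groups of people. Only the second contrast is the primary hypothesis, and the text does not say which of the two N = 12 serves.

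The scale does not match either. The endpoint is a placebo-compared AUC, while the inputs are oxytocin concentrations, one in pg/mL and one in pmol. The variance of a between-group test on AUC(MDMA) minus AUC(placebo) depends on the SD of that difference across people. The protocol gives neither that SD nor the correlation needed to approximate it, and it does not say whether ± is an SD or an SEM.

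What is at stake is how a null result would be read. Section 7.1 says the study should clarify whether these patients have an oxytocin deficiency. A non-significant result from a trial labelled as having 90% power would be taken as evidence against a 30% deficit. Section 5.1 does not support that inference.

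**Working it through.** **Inputs (section 5.1 unless noted).** MDMA 809 ± 64; placebo 259 ± 62; 28 healthy adults; 30% reduction; alpha 0.05; power 90%; 12 evaluable, 15 recruited. The synopsis gives 15 + 15, so 12 is read as per group.

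**Assumptions.** Both means are in the same unit; the SD is the same in patients and controls; tests are two-sided (the alternative is worded both as lower and as not zero); power comes from the noncentral t distribution.

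**1. The plan's own figures.** The drop-out step reproduces: 12 / (1 − 0.20) = 15. N = 12 does not.

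- *± as SD.* No variant tried, within-subject or between-group, needs more than 8 (pairs, or per group).
- *± as SEM, between groups.* The 30% effect needs 42 per group (step 2).
- *± as SEM, within subject.* Values near 12 appear only when a correlation is supplied that the protocol does not give. For example, an increase of 0.7 × (809 − 259) = 385 needs 14 pairs at correlation 0.25 and 11 at 0.5. The full increase of 550 needs 10 pairs at correlation 0.

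**2. Between-group test on the MDMA level.** Effect = 0.30 × 809 = 242.7.

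- *± as SEM.* SD = 64 × √28 = 338.7, so d = 242.7 / 338.7 = 0.717. Power is 38.9% with 12 per group and 47.4% with 15; 90% needs 42 per group.
- *± as SD.* SD = 64, so d = 242.7 / 64 = 3.79. Three per group give 92.7%; with 12 per group power is above 99%.
- *Break-even.* For 90% power on 242.7 the SD may be at most about 175 (12 per group) or 198 (15 per group). The protocol states neither value.

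**3. Placebo-corrected difference, SEM reading.** This is closer in form to the endpoint, but still concentrations and not AUC. Placebo SD = 62 × √28 = 328.1. SD of the difference = √(338.7² + 328.1² − 2ρ × 338.7 × 328.1), where ρ is the assumed MDMA-placebo correlation.

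| ρ (assumed) | SD of difference | Power for 242.7, 15 per group | Power for 165, 15 per group |
|---|---|---|---|
| 0 | 472 | 28% | 15% |
| 0.5 | 333 | 49% | 26% |
| 0.8 | 211 | 86% | 54% |

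The last column applies the 30% to the placebo-corrected increment: 0.30 × (809 − 259) = 165. For 242.7, 90% power needs ρ of about 0.82 with 15 per group, or about 0.86 with 12.

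**4. Placebo-corrected difference, SD reading.** At ρ = 0 the SD is √(64² + 62²) = 89. Power with 12 per group is 99% or more for both 242.7 and 165.

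**5. What can be stated without knowing the SD.** With 15 per group and two-sided 0.05, the detectable standardised difference is 1.23 at 90% power and 1.06 at 80%.

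**The case against.** The strongest reply is that the shortfall is conditional. If ± is an SD, the design is far larger than it needs to be, and nothing in the protocol rules that out. This stands. A reader might infer that the trial is underpowered for its primary comparison, but the documents do not support that as a flat statement. The SEM reading is more plausible, because under the SD reading the planned number would be several times what is needed. Plausibility is not a definition, however.

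A second reply is that N = 12 may be sound for the target actually named, an increase after MDMA, with a moderate within-subject correlation left unstated. This is fair: step 1 shows values either side of 12. It makes the fault a misdirected target with an undeclared assumption and not an arithmetic slip. It does not make the figure relevant to the group comparison.

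A third point concerns the synopsis remark that "the sample size is reduced as the inter-individual variability is reduced". A reader might take this as a claim that the cross-over makes the patient-control comparison efficient. The protocol does not say so. The remark is general, and section 3.3 separates the within-subject from the between-subject comparison. It is no part of this point.

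**Conclusion.** The concern holds as a statement about what has been shown. The 90% power in section 5.1 belongs to a within-subject increase, rests on concentrations with mixed units and an undefined ±, and is not demonstrated for the between-group AUC comparison. This does not depend on how ± is read.

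The size of any shortfall does. On the MDMA level, for a 30% reduction, the SEM reading gives 39% to 47% power across 12 to 15 per group, and the SD reading gives more than 99%. On the placebo-corrected difference under SEM, 15 per group give 28% to 86% over assumed correlations from 0 to 0.8. All of these use concentration figures as a stand-in for the AUC, because the protocol gives no AUC variance.

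It is also tempting to turn the detectable standardised difference into a percentage reduction with the SD of the MDMA concentration. That SD is neither placebo-corrected nor on the AUC scale, so the conversion is not supported.

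**What to change.** In section 5.1 and the synopsis:

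1. Remove the 90% power statement as support for the primary comparison, or confine it explicitly to MDMA against placebo within subjects and declare the correlation used.
2. State whether ± is an SD or an SEM, and give both means in one unit.
3. Take the SD of AUC(MDMA) minus AUC(placebo) from the 28-adult data, if available.
4. Restate power for the between-group contrast at the planned 15 evaluable per group. Suggested text: *With 15 evaluable participants per group and a two-sided alpha of 0.05, the comparison of patients with controls has 90% power for a standardised difference of 1.23 and 80% power for 1.06.*
5. Express this as a percentage reduction only once the SD of the AUC difference is known.

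The cost is text only. No additional participants are needed, but the stated power may become less favourable.

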### **5.2. Handling of missing data and drop-outs**

No data imputation is foreseen for missing data. Subjects will be enrolled and any drop-outs during the study replaced to reach a final study sample of at least 30 subjects. Any drop-out will be replaced by recruitment of new subjects.

## 6 REGULATORY ASPECTS AND SAFETY

### 6.1. Local regulations / Declaration of Helsinki

This study is conducted in compliance with the protocol, the current version of the Declaration of Helsinki, the ICH-GCP the HRA as well as other locally relevant legal and regulatory requirements.

### 6.2. (Serious) Adverse Events

An **Adverse Event (AE)** is any untoward medical occurrence in a patient or a clinical investigation subject which does not necessarily have a causal relationship with the trial procedure. An AE can therefore be any unfavourable or unintended finding, symptom, or disease temporally associated with a trial procedure, whether or not related to it.

A Serious Adverse Event (SAE) (ClinO, Art. 63) is any untoward medical occurrence that

- Results in death or is life-threatening,
- Requires in-patient hospitalization or prolongation of existing hospitalization,
- Results in persistent or significant disability or incapacity, or
- Causes a congenital anomaly or birth defect

Both Investigator and Sponsor-Investigator make a causality assessment of the event to the trial intervention, (see table below based on the terms given in ICH E2A guidelines). Any event assessed as possibly, probably or definitely related is classified as related to the trial intervention.

| Relationship                                                                            | Description                                                                                                               |
|-----------------------------------------------------------------------------------------|---------------------------------------------------------------------------------------------------------------------------|
| Definitely                                                                              | Temporal relationship
Improvement after dechallenge*
Recurrence after rechallenge
(or other proof of drug cause) |
| Probably                                                                                | Temporal relationship
Improvement after dechallenge
No other cause evident                                          |
| Possibly                                                                                | Temporal relationship
Other cause possible                                                                             |
| Unlikely                                                                                | Any assessable reaction that does not fulfil the above conditions                                                         |
| Not related                                                                             | Causal relationship can be ruled out                                                                                      |
| *Improvement after dechallenge only taken into consideration, if applicable to reaction |                                                                                                                           |

Both Investigator and Sponsor-Investigator make a severity assessment of the event as mild, moderate or severe. Mild means the complication is tolerable, moderate means it interferes with daily activities and severe means it renders daily activities impossible.

#### **Reporting of SAEs** (see ClinO, Art. 63)

All SAEs are documented and reported immediately (within a maximum of 24 hours) to the Sponsor-Investigator of the study.

If it cannot be excluded that the SAE occurring in Switzerland is attributable to the intervention under investigation, the Investigator reports it to the Ethics Committee via BASEC within 15 days.

#### **Follow up of (Serious) Adverse Events**

Following a comprehensive baseline evaluation, each patient's safety will be monitored with periodic record and evaluation of all treatment-emergent AEs.

One evidence of a clinical abnormality is noticed, the condition will be treated while trying to determine its cause. The patient will then be followed until the condition resolves or becomes chronic or stable. Patients will be instructed about possible acute AEs. If adverse events are observed, the participants are promptly treated according to standard of care.

#### **6.3. (Periodic) safety reporting**

An annual safety report (ASR/DSUR) is submitted once a year to the local Ethics Committee by the Investigator (ClinO, Art. 43 Abs).

#### **6.4. Radiation**

N/A.

#### **6.5. Pregnancy**

In case of pregnancy, study visit will not be started (see exclusion criteria). Pregnancies during the study will be reported within a maximum of 24 hours to the Sponsor-Investigator, and patient is withdrawn, and outcome of the pregnancy is followed up. An impairment of the sperm cells cannot be ruled out; therefore, patients and healthy participants must use a double contraceptive method (e.g. condom and pill) during the study and until one month afterwards.

#### **6.6. Amendments**

Substantial changes to the study setup and study organization, the protocol and relevant study documents are submitted to the Ethics Committee for approval before implementation. Under emergency circumstances, deviations from the protocol to protect the rights, safety and well-being of human subjects may proceed without prior approval of the Ethics Committee. Such deviations shall be documented and reported to the Ethics Committee as soon as possible.

Substantial amendments are changes that affect the safety, health, rights and obligations of participants, changes in the protocol that affect study objective(s) or central research topic, changes of study site(s) or of study leader and sponsor (ClinO, Art. 29).

#### **6.7. (Premature) termination of study**

The Sponsor-Investigator may terminate the study prematurely according to certain circumstances, e.g.

- Ethical concerns,
- Insufficient participant recruitment,
- When the safety of the participants is doubtful or at risk (e.g. when the benefit-risk assessment is no longer positive),
- Alterations in accepted clinical practice that make the continuation of the study unwise, or
- Early evidence of harm or benefit of the experimental intervention

Upon regular study termination, the Ethics Committee is notified via BASEC within 90 days (ClinO, Art. 38).

Upon premature study termination or study interruption, the Ethics Committee is notified via BASEC within 15 days (ClinO, Art. 38).

Please refer to [www.swissethics.ch](http://www.swissethics.ch) for a template concerning the notification of completion, discontinuation or interruption of the clinical trial.

All biological materials and health-related data will not be anonymized upon end of data analysis.

#### **6.8. Insurance**

Insurance will be provided by the Sponsor. A copy of the insurance certificate is filled in the investigator site file and trial master file.

## 7 FURTHER ASPECTS

### 7.1. Overall ethical considerations

This study will identify the role of OT in patients with central diabetes insipidus. Recent findings have suggested low OT levels in relation to increased psychopathology in patients with central diabetes insipidus. However, OT measurements are difficult, and no provocation test is yet available. This study will improve the pathophysiological implications of OT in patients with central diabetes insipidus by clarifying whether these patients indeed have OT deficiency. As standard OT measurements are unreliable and as for other pituitary hormones provocation tests are used, this study will explore whether MDMA can be used as provocation test for OT in patients with central diabetes insipidus and healthy controls. Future studies could consider interventional studies using OT application to reduce pathophysiology in patients with central diabetes insipidus and ultimately increase their quality of life.

The cross-over design with a washout period of at least two weeks is considered appropriate as first, no residual effects of MDMA is expected to be present after two weeks. Furthermore, the cross-over design allows a lower sample size as for the reduced inter-individual variability. In order to increase the understanding of the pathophysiology of OT and MDMA in patients with central diabetes insipidus it is crucial to compare the values to healthy controls. Only with these two study populations can we conclude how OT is stimulated following MDMA and whether an OT deficiency is present in patients with central diabetes insipidus.

### 7.2. Risk-benefit assessment

Trained study personnel will place venous accesses, perform intervention and collect blood samples. The frequency of the following possible side effects corresponds to the international guidelines of MedDRA. “Very common” corresponds to ( $\geq 10\%$ ), “common” (1-10%), “uncommon” (0.1-1%), “rare” 1/1000-1/10'000), and “very rare” ( $< 1/10'000$ ).

Blood sampling: At the injection sites for the venous catheter, small bruises can occur, but these will heal in a few days. In rare cases, vein occlusion or inflammation of the injection site may occur. If this is the case, the patient or healthy participant will be asked to report this immediately.

Psychopathological questionnaires: Patients or healthy participants do not have to answer any of the questions asked if they do not want to. If there is an emotional burden during the session /in-between the sessions or if there is a need for information or advice, the study physician can be contacted for further information and support.

MDMA: Several studies in healthy subjects with a single dose of MDMA has been conducted frequently and shown to be safe in controlled settings [33, 34, 38, 43, 51, 68–71]. This

considerable body of evidence indicates that the likelihood for significant toxicity from doses of MDMA such as the one to be used in the present study and in controlled settings is very low. Common moderate acute adverse effects can be increased jaw muscle tension, dry mouth, dizziness, palpitations, tremor, nausea, headache, insomnia and transient anxiety in approximately 10% of subjects [43, 69, 72].

The main expected acute adverse effects are consistent with moderate sympathomimetic toxicity including moderate hypertension, tachycardia and a raise in body temperature. Patients and healthy participants will be screened with an ECG and standardized blood pressure measurement; any pathological finding will be assessed by the study physician. Closer monitoring will be implemented if blood pressure values exceed 180/120 mmHg systolic blood pressure ( $P_{\text{sys}}$ ). Treatment of a hypertensive reaction ( $P_{\text{sys}} > 220$  mmHg) may include administration of oxygen, nitrates and nifedipine, or esmolol and/or transfer to medical services (Emergency Department). In the case of angina pectoris, oxygen is given, and ECG monitoring is initiated, and cardiac enzymes will be measured followed by consultation with the cardiologist on call. Cardiac arrest triggers immediate cardiopulmonary reanimation and defibrillation by the study team (defibrillator on site) and call to the ambulance (0144). An increase in body temperature of 0.5°C are expected after MDMA administration [43, 72, 73]. If body temperature rises by more than 1.5°C appropriate treatment including hydration and cooling will be initiated [56].

Ecstasy use has been associated with both dehydration and hyperhydration leading to hyponatremia [56, 74–77]. Subjects will be encouraged to drink to thirst, but in general no less than 1 and no more than 3 l during one session. Serum sodium levels checked as described in Table 2 at timepoint 0min, 90min, 120min, 150min, 180min and 300min. If symptoms of hyponatremia such as confusion or vomiting present between these intervals, subjects will be further examined and sodium levels rechecked. Participants will be informed of these symptoms and encouraged to report if these symptoms occur following the study visit.

Acute psychological distress was observed to be minimal; no lasting biological or psychological injury is expected. There is no indication that administration of MDMA in a controlled setting has any adverse effects on cognitive function [30, 72, 85].

Recreational use of Ecstasy has been linked to reversible neurotoxicity [78, 79], especially when the drug is taken frequently and in high doses [80]. In contrast, imaging studies do not indicate any changes after moderate MDMA use [35]. Several studies document no lasting effects of Ecstasy in moderate Ecstasy users [53, 78, 81]. No changes in serotonin transporter density were seen using positron emission tomography and [11C]-McN5652 four weeks after MDMA

administration (1.5-1.7 mg/kg) in MDMA-naive human volunteers [86,87]. The use of MDMA in controlled settings is considered safe with regard to neurotoxic effects [47, 82].

MDMA has rarely been associated with liver toxicity but often under overdose and not in controlled clinical setting [56]. Liver enzymes will be measured at the screening visit and pathological results will be excluded regarding the exclusion criteria.

The participants will be under continuous medical supervision and closely monitored during MDMA application and until the acute effects completely subsided; expected within 6h for MDMA [74]. Subjects with known risk factors for future drug abuse including current major depression, psychotic disorder and anxiety disorders [83] and prior drug dependence or other relevant illicit drug use [84] will be excluded from the study. Illicit drug use will also be monitored during the study using repeated urine drug screens before both main sessions.

Six hours after stimulation participants will be allowed to return to their home alone. If effects persist, the night is spent at the research facility. In the case of unexpected prolonged or severe adverse reactions subjects will remain in the hospital and are monitored as long as necessary. Subjects will be provided with the phone number of the study physicians in case of an emergency between/after study sessions.

MDMA is expected to produce sequelae (1-3 days post MDMA) including difficulty concentrating, irritability, or slightly depressed mood in about 10% of subjects [69]. Participants will receive a phone call 3 days after the intervention to assess mood changes and adverse events.

MDMA is neither mutagenic nor teratogenic and their chronic use is not associated with birth defects. Pregnant women are excluded from the study and pregnancy tests will be done before each test session. Effective birth control will be mandatory for female participants.

We do not expect immediate benefit to the study participants. Our data could clarify an OT deficiency in patients with central diabetes insipidus and give new information for further studies.

